#### - RTW

When measuring the effect of a RTW intervention, it can be expected to take actual RTW as an important outcome measure. For sick-listed employees full RTW and ending of the sickness absence period coincides, in principle. However, for the sick-listed temporary agency worker and the sick-listed unemployed worker moving from being sick-listed to end of sickness benefit does not automatically also mean full RTW. Because in most cases these workers have no workplace/employer to return to, the worker can report being fully recovered from illness or the insurance physician of the SSA can establish full recovery of functional limitations (assessed with regard to last/previous work) without actual RTW of the worker. Therefore, RTW is measured as a separate outcome measure. RTW is defined as: duration from the first day of reporting sick until actual first RTW in any type of paid work or work resumption with ongoing benefits. Since for the majority of these workers there is no workplace to return to, working in the same or different type of work(place) is classified as RTW.

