### Study population

The population in this study consists of temporary agency workers and unemployed workers, who live in the eastern part of the Netherlands and when sick-listed come under one of the five following front offices of the Social Security Agency: UWV Arnhem, UWV Apeldoorn, UWV Hengelo, UWV Nijmegen, or UWV Zwolle. The main inclusion criteria are: 1. being a temporary agency worker or unemployed worker; 2. being between 18 and 64 years of age; 3. being sick-listed between 2 and 8 weeks; and 4. having MSD as main reason for a sickness benefit claim. The main exclusion criteria are: 1. an accepted sickness benefit claim and being sick-listed for more than 8 weeks; 2. not being able to complete questionnaires written in the Dutch language; 3. having a conflict with the SSA or the Dutch Institute for Benefit Schemes (UWV) regarding a sickness benefit claim or a long-term disability claim, respectively; 4. the presence of a legal conflict, e.g. an ongoing injury compensation claim; and 5. an episode of sickness absence due to MSD within one month before the current sickness benefit claim. After inclusion and randomisation the insurance physician of the SSA is asked to identify workers with severe co-morbidity; i.e. terminal disease, serious psychiatric disorders, or serious cardio-vascular disease, since these are contra-indications for receiving the participatory RTW program. These participants are prevented from starting with the participatory RTW program. However, following the intention-to-treat principle, they remain in the allocated study group (intervention or control). For an overview of all inclusion and exclusion criteria, see table 1.

**Table 1 T1:** Overview of inclusion and exclusion criteria

Inclusion criteria
• temporary agency worker or unemployed worker
• age between 18 and 64 years
• sick-listed between 2 and 8 weeks
• MSD complaints as main reason for reporting sick
• able to complete questionnaires written in Dutch

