### Recruitment of participants

For the recruitment of participants the database of the SSA is used. When reporting sick not only personal data, but also the reason for this, i.e. the health problem, is registered (using codes) in a computerised client record system. Based on a weekly query of this record system, all temporary agency workers and unemployed workers who are sick-listed between one and two weeks due to MSD, and live in the eastern part of the Netherlands receive a letter from the insurance physician of the SSA, on behalf of the researchers. The aim of this letter is to give information about the study and to ask for their participation. In addition, they also receive an information flyer with more details about the study, a screening questionnaire, and a return envelope for the screening questionnaire. The reason for approaching potential participants in the second week of sick leave is the time period in which a RTW action plan has to be made, i.e. 8 weeks after the first day of reporting sick. This is obligated according to the Dutch Improved Gatekeeper Act. Furthermore, it has been shown that early RTW intervention is important to prevent long-term work disability[4,32-34].

Temporary agency workers and unemployed workers who return the questionnaire, and meet the criteria (being temporary agency worker or unemployed worker, and still sick-listed), and indicate that they are willing to participate are contacted by the researchers by telephone. In this telephone call additional information is given about the content of study and the implications of participation. Using the formulated inclusion and exclusion criteria, the eligibility of the worker is checked. If the temporary agency worker or unemployed worker meets all selection criteria and still wants to participate, an intake appointment with the research assistant is planned at one of the UWV front offices. The worker receives a confirmation of this appointment by postal mail, including a detailed information brochure about the study. During the meeting with the research assistant the worker gives informed consent, fills in the baseline questionnaire, and randomisation is performed.

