#### - Direct and indirect costs

Direct costs are paid by the SSA for interventions regarding vocational rehabilitation support, e.g. training/education, for interventions aimed at health promotion, e.g. physical therapy (graded activity) and/or psychological help, or interventions aimed at RTW, e.g. searching for a (temporary) workplace by contracting a vocational rehabilitation agency or temporary placement in work with a willing employer and with an ongoing benefit. Information regarding direct costs is collected from the SSA database and the worker's files after one year of follow-up.

Indirect costs are related to costs due to paid sickness benefit for the sick-listed workers with MSD. When looking at sick-listed temporary agency workers and sick-listed unemployed workers, loss of productivity is not part of the indirect costs. When reporting sick the temporary agency workers immediately falls under the SSA for substituted income, i.e. the sickness benefit. The temporary agency replaces the sick-listed temporary agency worker with a healthy worker at the company/workplace concerned with no productivity loss as a result. Therefore, indirect costs with regard to sick-listed temporary agency workers are the sickness benefit costs paid by the SSA. However, this does not apply to unemployed workers. These workers have no work(place), i.e. there is no productivity. As a consequence, being sick-listed does not result in a productivity loss. Another important fact is that an unemployed worker receives an unemployment benefit. After reporting sick with acceptance of the sickness benefit claim by the SSA, the sick-listed unemployed worker receives a sickness benefit instead of an unemployment benefit. However, the amount of these benefits can differ as this is established using different income conditions. As a result, the sickness benefit can be more than the unemployment benefit. From this perspective, the additional benefit costs are considered indirect costs in this study. Data on paid benefits are collected from the SSA database after the one-year follow-up. Cost-benefit evaluation of the new RTW program is part of this study and will be discussed below.

An overview of the outcome measures and the measurement instruments used, including a time path for all measurements, is presented in table 2.

**Table 2 T2:** Overview of measurements and time path

Measurement	Time path				
	**Baseline**	**3 months**	**6 months**	**9 months**	**12 months**

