### Prognostic measures

At baseline information is gathered regarding demographic variables, such as gender, age, and level of education. Also, information regarding last work, e.g. type of previous work and number of working hours, and the work status (working or not working) directly prior to the baseline measurement is collected. This is partly based on findings in the international literature [47-49], indicating that the work status before sickness absence is a prognostic factor for the duration of sick leave and work disability.

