### Sample size

In this study the primary outcome measure is duration of the sickness benefit period. Recurrence of sickness absence (due to the same or related MSD) with an accepted sickness benefit claim within 4 weeks after ending of the previous sickness benefit is considered as belonging to the preceding sickness benefit period. As a starting-point for calculating the sample size we assume that a Hazard Ratio (HR) of 2.0 is the minimal clinical and societal relevant ratio, indicating that temporary agency workers and unemployed workers in the intervention group end their sickness benefit period twice as quickly compared to the workers in the control group. This HR is based on comparable studies on sickness absence and RTW of short-term sick-listed employees[25,46,53-55]. Assuming that the sickness benefit will end for 2/3 of the participants during the one-year follow-up period, and based on a power of (1-β =) 0.80 and a two-sided significance level of 0.05 (α) a sample size of 100 participants (n = 2 × 50) is needed[56]. Since there is a continuous registration of sickness benefit duration by the SSA, a high loss to follow-up with regard to the primary outcome is not expected. However, based on comparable research[57,58] loss to follow-up of 10% is taken into account. This results in 110 participants (n = 2 × 55) to be included in the study. Next, potential clustering of cases assessed by the same insurance physician is taken into account, since the insurance physician plays a key role in acceptance of the sickness benefit claim and the assessment of (sufficient) recovery of functional limitations. For this calculation an ICC of 0.05[25,46] is used and a minimal number of clusters of 10 (i.e. 5 front offices with at least 2 participating insurance physicians at each office). This results in 160 participants (n = 2 × 80) to be enrolled in the study.

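### Time to first RTW can count work resumed before randomisation, which would dilute this secondary outcome; the definition should set such resumptions aside (low priority)

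*Protocol article*

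**What the plan says.** The protocol article, Outcomes, RTW, defines the outcome as "duration from the first day of reporting sick until actual first RTW in any type of paid work or work resumption with ongoing benefits". This fixes both the start of the clock and the event, and the event includes work done while benefit continues.

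Under Study population, a main inclusion criterion is "being sick-listed between 2 and 8 weeks". Under Recruitment of participants, the order at intake is given: "During the meeting with the research assistant the worker gives informed consent, fills in the baseline questionnaire, and randomisation is performed". The clock has therefore been running for some weeks at allocation. The work-related check before the telephone call is that respondents "meet the criteria (being temporary agency worker or unemployed worker, and still sick-listed". Neither the criteria in the text nor Table 1 exclude a sick-listed worker who has already resumed some work.

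Being on benefit and being at work can coexist. The section on direct and indirect costs lists "temporary placement in work with a willing employer and with an ongoing benefit" among the interventions the agency may pay for.

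On baseline work status the article gives two descriptions. Prognostic measures says that "the work status (working or not working) directly prior to the baseline measurement is collected". Table 2 lists the item as status before the sick report.

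**The concern.** Take a worker who resumes some work with ongoing benefit in week 3 and is randomised in week 6. By the definition, the first RTW is dated to week 3. It happened before allocation, so it can differ between arms only by chance. It still counts as that worker's one event, and nothing the program achieves later for that worker can appear in this outcome. Each such event adds to the event count without adding contrast, so the estimated effect moves towards no difference.

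The primary outcome has the same time origin but not the same exposure. Its event is the end of benefit, and benefit must still be running at entry. RTW lacks that protection because resumption with ongoing benefit is itself the event.

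At stake is a secondary outcome, but one close to the program's purpose. The article measures it separately because the end of benefit need not mean a return to work.

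**Working it through.** **The plan's own figures.** No effect size or sample size is given for RTW. The Sample size section, for the primary outcome, states "we assume that a Hazard Ratio (HR) of 2.0 is the minimal clinical and societal relevant ratio", with 2/3 of participants having the event in one year, power 0.80 and two-sided alpha 0.05. These reproduce:

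- Events = 4(1.96 + 0.8416)² / (ln 2)² = 65.3, so 66.
- 66 / (2/3) = 99, against the stated 100.
- 100 × 1.10 = 110 for loss to follow-up.
- Design effect 1 + (10 − 1) × 0.05 = 1.45, taking 100/10 = 10 participants per physician. 110 × 1.45 = 159.5, so 160.

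None of this depends on how RTW is timed. The hazard ratio of 2.0 and the 2/3 are borrowed below only to give a scale.

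**Assumptions for the illustration.** A share q of participants resumes work between the sick report and randomisation, equally in both arms. The others have a true post-randomisation hazard ratio of 2.0, and 2/3 of them have an event. The analysis is a Cox model. The documents give no value for q and name no model for time to RTW.

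**Event-weighted approximation.** Events before randomisation carry a log hazard ratio of 0, and later ones carry ln 2 = 0.693.

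- Share of events before randomisation: s = q / [q + (1 − q) × 2/3]
- Diluted hazard ratio: exp[(1 − s) × 0.693]

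For q = 10%: s = 0.10 / (0.10 + 0.60) = 0.143, and exp(0.857 × 0.693) = 1.81.

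A simulation served as a check: 400,000 participants per scenario, entry uniform over 2 to 8 weeks, constant hazards, 52 weeks of follow-up after randomisation.

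| q | s | HR, approximation | HR as written, simulated | HR from randomisation, prior resumers set aside, simulated |
|---|---|---|---|---|
| 0% | 0 | 2.00 | 2.00 | 2.00 |
| 5% | 0.073 | 1.90 | 1.91 | 2.01 |
| 10% | 0.143 | 1.81 | 1.80 | 1.99 |
| 20% | 0.273 | 1.66 | 1.65 | 2.00 |

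The first row isolates the time origin. With no prior resumers, starting the clock at the sick report leaves the hazard ratio at 2.0.

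**Power.** Loss and clustering reduce 160 to roughly the 100 independent participants the plan started from. With D events among 100, power ≈ Φ(√(D/4) × ln HR − 1.96).

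| q | As written: D, power | Prior resumers set aside: D, power |
|---|---|---|
| 0% | 66.7, 81% | 66.7, 81% |
| 5% | 68.3, 76% | 63.3, 79% |
| 10% | 70.0, 70% | 60.0, 77% |
| 20% | 73.3, 58% | 53.3, 72% |

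The column for the change also falls, because workers already back at work contribute nothing to learn from. Only the gap between the two columns is due to the definition.

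**The case against.** **Prior resumers may be rare.** No passage says that any exist. Entrants must still be sick-listed, which largely removes ordinary full return to paid work and leaves resumption with ongoing benefit as the open route. The RTW section itself notes: "Because in most cases these workers have no workplace/employer to return to". The first assessment by the insurance physician is in principle at 6 weeks, and the action plan is due at 8 weeks, so agency-arranged placements before randomisation should be few. This stands. It limits the size of the problem but does not remove the rule that would count such events.

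**The time origin is harmless.** This also stands. A reader might infer that counting from the first sick day biases RTW, or biases the primary outcome as well. The documents and the arithmetic do not support either reading: with no prior resumers there is no bias, and benefit must still be running at entry.

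**The protocol did not clearly foresee the case.** A reader might take the RTW mark at baseline in Table 2 as a sign that baseline returns were expected. The same table marks duration and total days of sickness benefit at baseline, so the mark shows little. The work-status item is equally weak evidence: the article justifies it by literature on status before sickness absence, and Table 2 labels it that way.

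**The analysis is assumed.** Kaplan-Meier and Cox are named for sickness benefit only, and risk-set details are normally left to an analysis plan. That is fair for the model, and no fault is found with its absence. The point rests on the outcome definition, which the article does state. Counting events that precede allocation dilutes any comparison of time to first RTW.

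**Conclusion.** The point holds in a limited form. As defined, time to first RTW counts any resumption with ongoing benefit since the sick report, and eligibility does not exclude workers who resumed before randomisation. Where such workers exist, the RTW contrast is diluted towards the null.

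The size cannot be fixed from the documents. Under the assumptions above, the hazard ratio would be about 1.9 at 5% prior resumption, 1.8 at 10% and 1.65 at 20%, against a true 2.0, with no bias at 0%. The lower end seems more plausible in this population. A reader might infer a large loss of power from the higher proportions, but nothing in the documents supports a particular proportion or states an RTW effect.

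One secondary outcome is affected, the error is towards no effect, and the primary analysis is untouched. Low priority.

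**What to change.** - In the RTW definition, count time from randomisation. Alternatively, keep the sick-report time scale and let each worker enter the risk set at randomisation (delayed entry).
- Restrict the time-to-RTW analysis to workers with no work resumption between the sick report and randomisation. Selection on a fact settled before allocation keeps the randomised comparison intact.
- Report the number set aside in each arm.
- Reconcile Prognostic measures with Table 2 on which work status is recorded, and make sure that a baseline item captures any resumption since the sick report. Without that item the restriction cannot be applied reliably.

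The cost is a change of wording and, if the present item records only status before sickness, one added baseline question. The dates of the sick report and of randomisation are already known. The downside is small: workers already back at work do not contribute to this one secondary outcome.

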#### - Total number of days of sickness benefit

The total number of days of sickness benefit will be measured for the whole one-year follow-up period. For calculation of the total duration of sickness benefit awarded sickness benefit claims are only included when due to same (or related) MSD.

#### - Severity of MSD

Severity and changes in MSD are measured with the Dutch version of the Nordic Musculoskeletal Questionnaire (DMQ)[36]. In addition, musculoskeletal pain intensity is measured using the Von Korff[37].

#### - Functional status

Functional status, i.e. perceived functional impairments in daily life, is measured using the Dutch translation of the RAND-36[38,39].

#### - General health

General health is measured using the Dutch translation of the RAND-36. Quality of life is measured using the Dutch translation of the Euroquol questionnaire[40].

#### - Coping

Pain coping is measured using the Pain Coping Inventory Scale (PCI)[41].

#### - Attitude, Social Influence and self-Efficacy (ASE) determinants

In line with the development of a participatory RTW program for sick-listed employees with common mental disorders (CMD)[42], the Attitude-Social influence-self-Efficacy (ASE) model was chosen as underlying theoretical framework [43-45] for the development of the new participatory RTW program for sick-listed temporary agency workers and sick-listed unemployed workers. For the developed RTW intervention for CMDs questions about attitude, social influence, self-efficacy, barriers and facilitators were formulated and measured on bipolar five-point Likert scales[46]. This questionnaire is also used in this study.

#### - Direct and indirect costs

Direct costs are paid by the SSA for interventions regarding vocational rehabilitation support, e.g. training/education, for interventions aimed at health promotion, e.g. physical therapy (graded activity) and/or psychological help, or interventions aimed at RTW, e.g. searching for a (temporary) workplace by contracting a vocational rehabilitation agency or temporary placement in work with a willing employer and with an ongoing benefit. Information regarding direct costs is collected from the SSA database and the worker's files after one year of follow-up.

Indirect costs are related to costs due to paid sickness benefit for the sick-listed workers with MSD. When looking at sick-listed temporary agency workers and sick-listed unemployed workers, loss of productivity is not part of the indirect costs. When reporting sick the temporary agency workers immediately falls under the SSA for substituted income, i.e. the sickness benefit. The temporary agency replaces the sick-listed temporary agency worker with a healthy worker at the company/workplace concerned with no productivity loss as a result. Therefore, indirect costs with regard to sick-listed temporary agency workers are the sickness benefit costs paid by the SSA. However, this does not apply to unemployed workers. These workers have no work(place), i.e. there is no productivity. As a consequence, being sick-listed does not result in a productivity loss. Another important fact is that an unemployed worker receives an unemployment benefit. After reporting sick with acceptance of the sickness benefit claim by the SSA, the sick-listed unemployed worker receives a sickness benefit instead of an unemployment benefit. However, the amount of these benefits can differ as this is established using different income conditions. As a result, the sickness benefit can be more than the unemployment benefit. From this perspective, the additional benefit costs are considered indirect costs in this study. Data on paid benefits are collected from the SSA database after the one-year follow-up. Cost-benefit evaluation of the new RTW program is part of this study and will be discussed below.

An overview of the outcome measures and the measurement instruments used, including a time path for all measurements, is presented in table 2.

**Table 2 T2:** Overview of measurements and time path

Measurement	Time path				
	**Baseline**	**3 months**	**6 months**	**9 months**	**12 months**
	**(T0)**	**(T1)**	**(T2)**	**(T3)**	**(T4)**

*Prognostic measures*					
- Demographic variables (e.g. age, gender)	X				
- Last work (function, hours)	X				
- Work status before reporting sick	X				

					

*Primary outcome measure*					
- Duration of sickness benefit	X	X	X	X	X

					

*Secondary outcome measures*					
- RTW	X	X	X	X	X
- Total number of days of sickness benefit	X	X	X	X	X
- Severity of complaints (DMQ)	X	X	X		X
- Pain intensity (Von Korff)	X	X	X		X
- Functional status (RAND-36)	X	X	X		X
- General health (RAND-36)	X	X	X		X
- Quality of life (Euroqol EQ-5D)	X	X	X		X
- Coping (PCI)	X				
- ASE determinants (ASE questionnaire)	X	X			
- Direct and indirect costs					X
- Patient satisfaction (PSOHSQ)*		X			

* patient satisfaction with occupational health services is only measured in the intervention group (as part of the process evaluation)

